#### Sample size and power calculations

Hospitalizations are likely to dominate events in the composite endpoint of hospitalizations (excluding day-only hospitalizations), serious out-of-hospital events and deaths. Therefore hospitalization data were used to power the study, with the aim to detect a 25 % reduction in hospitalizations. The sample size and power calculations for the study were based on the Fisher’s exact test, as this is a conservative analysis and enables use of the Australian Institute of Health and Welfare data (AIHW) [47] that indicate a yearly risk of hospitalization of 62 % for women and 78 % for men aged 66 to 69, and 80 % and 115 % for women and men aged 70 to 74, respectively, using hospital separation data from 2003 to 2004. The AIHW data are for all hospitalizations. This study excludes day-only hospitalizations in the composite endpoint, but includes serious out-of-hospital events and deaths. Overall, we estimated that at least 70 % of the subjects in the control arm would have at least one event (either an overnight hospitalization, a serious out-of-hospital event or death) throughout the 48-month duration of the trial. With these assumptions, 80 % power and a 0.025 level of significance, to detect a 25 % reduction in hospitalizations requires 158 subjects per arm for analysis by a Fisher’s exact test of proportions. In order to provide for the loss of power due to patients discontinuing (at the most conservative, assuming a 40 % non-differential dropout from the intervention arms), the trial requires 792 subjects, or 264 subjects per arm. Regarding local feasibility, in 2008 there were 11,421 unplanned admissions via the emergency department at our institution (St George Hospital) alone for patients aged 60 years or older. The entire study area of southern Sydney has several public and private hospitals.

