### Outcomes

#### Primary outcome

The primary outcome is a combined endpoint of the total number of important clinical events, defined as: all overnight hospitalizations, all serious out-of-hospital events and death. Validation of hospitalizations or out-of-hospital events occurs by subject interview, and health-care provider and hospital records as close to real time as is possible. In addition, record linkage with Medicare Australia, Department of Veterans Affairs, Australian Institute of Health and Welfare and NSW Health during the study is another source of valid information on hospitalizations, health service utilization (including a record of all medical encounters) and deaths. Furthermore, an Independent Adjudication Committee (IAC) determines which out-of-hospital events are serious, and are therefore included in the primary combined outcome.

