#### Primary statistical analyses

There are two co-primary analyses because this is a three-arm, randomized controlled trial: e-PHF versus usual care and p-PHF versus usual care. Both analyses use the combined endpoint of deaths, hospitalizations (excluding day-only admissions) and adjudicated serious out-of-hospital events, and both use an adaptation of the Andersen-Gill formulation [43] of the proportional hazards model in order to capture possibly correlated events in the same subject. A robust variance estimate [44] will be used that takes into account the possibility of correlation of risk of multiple events within a subject by including an additional time-dependent covariate indicating whether the event was the first or subsequent event of its kind. The level of significance for each analysis is 0.025. This is an intention-to-treat analysis.

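### The 158 per arm (264 with dropout) powers a fall from 70 % to 52.5 % in subjects with any event, not the 25 % reduction in hospitalizations that the text claims

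*Protocol article*

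**What the plan says.** Under Sample size and power calculations, the Protocol article powers the trial on hospitalizations, "with the aim to detect a 25 % reduction in hospitalizations". The test is Fisher's "exact test, as this is a conservative analysis and enables use of the Australian Institute of Health and Welfare data". The control input is a person-level proportion over 48 months: "we estimated that at least 70 % of the subjects in the control arm would have at least one event". Power is set at 80 % and alpha at 0.025. The section concludes that "to detect a 25 % reduction in hospitalizations requires 158 subjects per arm for analysis by a" test of that kind. Allowing for 40 % dropout gives 264 per arm and 792 in all. The same section quotes national hospital separation figures of 62 % to 115 % by age and sex and calls them a yearly risk.

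Elsewhere the scale differs. Under Primary outcome: "The primary outcome is a combined endpoint of the total number of important clinical events". Under Primary statistical analyses, the two co-primary comparisons "both use an adaptation of the Andersen-Gill formulation [43] of the proportional hazards model in order to capture possibly correlated events", and "The level of significance for each analysis is 0.025".

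**The concern.** The outcome and its analysis concern how many events occur. The sample size concerns how many subjects have any event. A 25 % reduction means different things on the two scales: a subject whose expected count falls from four to three will usually still have at least one event. The text names the effect on the count scale, solves for it on the any-event scale, and neither prints the intervention-arm proportion nor converts between the two.

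The stake is how the result is read. If the trial is null, readers will take it that a 25 % reduction in hospitalizations was tested with 80 % power. The calculation shown does not support that.

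**Working it through.** **1. Reproduce the plan's figure.** Inputs from Sample size and power calculations: control proportion 0.70, relative reduction 25 %, power 80 %, alpha 0.025. The intervention proportion is not printed; 0.75 × 0.70 = 0.525 is inferred because it returns the stated number. Sidedness is not stated; the number reproduces as two-sided (z = 2.2414 and 0.8416).

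- Uncorrected n = [2.2414·√(2 × 0.6125 × 0.3875) + 0.8416·√(0.70 × 0.30 + 0.525 × 0.475)]² / 0.175² = 146.02.
- Continuity-corrected n = (146.02/4) × [1 + √(1 + 4/(146.02 × 0.175))]² = 157.2, so **158**.
- Exact Fisher power at 158 per arm, by enumeration: 80.3 %.
- 158/0.6 = 263.3, so **264**; 3 × 264 = **792**.

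The 25 % was therefore applied to the proportion of subjects with any event.

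**2. Convert to the event scale.** Assume the intervention multiplies every subject's event rate by the same ratio, and that rates vary between subjects with variance k (gamma, mean 1). The article does not give k; 0 to 2 is an assumed range.

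- Control mean count μ₀ giving 70 % with any event: −ln(0.3) = 1.204 for k = 0; (0.3⁻ᵏ − 1)/k otherwise.
- Proportion with any event at mean μ: 1 − e^(−μ) for k = 0; 1 − (1 + kμ)^(−1/k) otherwise.
- Example, k = 0: 0.75 × 1.204 = 0.903, and 1 − e^(−0.903) = 59.5 %. To reach 52.5 %, the rate ratio is −ln(0.475)/1.204 = 0.618.

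**3. Power for a rate ratio of 0.75.** The variance of the log rate ratio with robust standard errors is (1/μ₀ + 1/μ₁ + 2k)/n, with μ₁ = 0.75μ₀. Power = Φ(0.2877/SE − 2.2414).

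- Example, k = 0, n = 158: (0.8306 + 1.1074)/158 = 0.01227; SE 0.1108; power Φ(0.356) = 64 %.
- Example, k = 1, n = 264: (0.4286 + 0.5714 + 2)/264 = 0.01136; SE 0.1066; power Φ(0.457) = 68 %.

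| k | μ₀ | Any event at rate ratio 0.75 | Rate ratio needed for 52.5 % | Fisher power, 158 | Andersen-Gill power, 158 | Andersen-Gill power, 264 | n per arm for 80 % (Andersen-Gill) |
|---|---|---|---|---|---|---|---|
| 0 | 1.204 | 59.5 % | 0.618 | 35 % | 64 % | 87 % | 223 |
| 0.5 | 1.651 | 61.9 % | 0.546 | 20 % | 53 % | 78 % | 278 |
| 1 | 2.333 | 63.6 % | 0.474 | 12 % | 44 % | 68 % | 345 |
| 2 | 5.056 | 65.9 % | 0.339 | 6 % | 30 % | 49 % | 513 |

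Simulation at 158 per arm gave 64 %, 54 %, 45 % and 31 %. At 264 per arm it gave 88 %, 79 %, 69 % and 52 %.

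**4. Sensitivity.**

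- *Higher control mean.* The text says at least 70 %. With a mean of 2.0 events, power at 158 is 87 % for k = 0 and 59 % for k = 0.5. With a mean of 4.6 and k = 0.5 it is 76 %.
- *Dilution.* The 264 column assumes a full effect in everyone. If 40 % discontinued at once and gained nothing, the average rate ratio would be 0.6 × 0.75 + 0.4 × 1 = 0.85, and power at 264 would be 39 %, 31 %, 24 % and 16 % for k = 0, 0.5, 1 and 2. This is an extreme bound.
- *Other form of effect.* If 25 % fewer subjects have any event and counts among the rest are unchanged, both scales fall by 25 %. Robust variance is then [(1 + c)/0.70 − 1 + (1 + c)/0.525 − 1]/n, with c the squared coefficient of variation of the count among subjects with events. Power at 158 is 81 %, 59 %, 44 % and 29 % for c = 0, 0.25, 0.5 and 1.

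The calculations assume full follow-up, ignore truncation by death and omit the first-or-subsequent-event covariate.

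**The case against.** **The word conservative can be defended.** A reader might infer from the mismatch that the label is wrong. The figures do not support that. For the same proportional rate effect, Fisher's test has less power than the recurrent-event analysis in every row of the table (35 % against 64 % at k = 0). The article also does not say that Fisher is conservative relative to Andersen-Gill; that comes from context. The order can reverse only under a different form of effect, such as the last one in the sensitivity checks. This objection stands.

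**There is no arithmetic error, and the basis is partly disclosed.** The numbers 158, 264 and 792 all reproduce, and the text mentions at least one event and a test of proportions. This stands too. What remains is that the effect is labelled as something else and 52.5 % is never printed.

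**158 is not the planned analysis set.** The statistical analysis section includes all randomized subjects, and the Discussion says hospitalizations and deaths will be ascertained despite withdrawal. So 264 per arm is the relevant number. This stands in part: the extra subjects were added to offset power lost through discontinuation, and under intention-to-treat that loss appears as a diluted effect rather than missing subjects.

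**The inputs may be pessimistic.** The population is enriched for heavy users of care, and the Discussion reports later separation rates 12.9 % to 28.8 % higher. With an assumed mean of 2.48 events, power at 264 without dilution is over 99 %, 87 % and 69 % for k = 0, 0.5 and 1. This is fair: the answer turns on quantities the article does not give.

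**The separation figures are a wording matter.** A reader might infer that they feed Fisher's test directly. They do not: the 70 % is a separate estimate, and no number is shown to change. Still, 115 % cannot be a risk.

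**Conclusion.** The point holds as a mislabelled effect and an unsupported power statement. The 158 per arm is correct for 70 % against 52.5 % with any event. It does not establish 80 % power for 25 % fewer hospitalizations under the planned analysis. With exactly 70 % of controls affected and a proportional rate effect, power at 158 is 64 % at best and 30 % at k = 2. At 264 without dilution it runs from 87 % to 49 %.

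A reader might conclude that the trial is shown to be underpowered. The documents do not support that: the result depends on the control mean count, k, dilution and the form of the effect, and some plausible combinations exceed 80 % at 264 per arm. The shortfall is a range, not a fixed figure. This should be fixed, but it does not call the design into question.

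**What to change.** In Sample size and power calculations:

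- State that 158 per arm detects a fall from 70 % to 52.5 % in subjects with at least one event over 48 months (two-sided 0.025, if that was intended).
- Do not claim 80 % power for a 25 % reduction in hospitalizations on that basis.
- Report Andersen-Gill power at 264 per arm for a rate ratio of 0.75, over stated ranges of control mean count, between-subject variance and dilution from discontinuation. Blinded pooled counts can inform the first two.
- Keep the word conservative only for Fisher's test against the recurrent-event test under the same proportional rate effect, not as assurance that 158 per arm secures 80 % power.
- Describe the national figures as separations per 100 persons per year, not as a risk.

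The cost is rewording and one recalculation. The stated power may become less favourable. Enrolment and the primary analysis do not change.

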### Methods: statistical analysis plan

All analyses will include all subjects randomized regardless of whether or when they may have withdrawn from the study. Therefore, for the primary and secondary objectives, the analysis will follow intention-to-treat principles. However, a completer’s analysis which is a comparison based on random allocation of subjects with complete data at the end of the trial, will also be undertaken as well as an as-treated complier’s analysis, which is based on the actual intervention and for how long it was utilized. The completer’s analysis and the as-treated analyses are exploratory analyses only.

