Strictly masked treatment allocation (by remote computer) is employed. A variety of trial conduct features were used to limit bias present because full blinding was not feasible in this trial. Firstly, the primary endpoint was made objective (overnight hospitalization and death) and will be ascertained regardless of whether a patient has withdrawn from the study. Medically important serious out-of-hospital events are expected to be rare and will all be independently adjudicated. Because the most important secondary endpoint, quality of life, may be prone to ascertainment bias, we were particularly attentive to balancing patient interactions and contact across all three arms regarding the six-monthly data collection through questionnaires of quality-of-life measures, PHF acceptability and health service utilization, and periodic telephone inquiries to confirm events such as hospitalizations, out-of-hospital events and adverse events that may need adjudication. We are also attempting to obtain post-discontinuation quality-of-life measures and interviews in patients choosing to drop out of the trial. Although study personnel clearly explain that the study is a randomized trial and whether the patient receives a PHF or not is determined by a random process, patients may nonetheless agree to be recruited hoping to be randomized to a PHF arm, and later withdraw consent and drop out of the trial if they are randomized to usual care.

Possibly, a tendency to better health attention generally for the patients in the PHF arms could skew the hospitalization rate in either direction. However, merely undertaking this trial will yield a wealth of experience with the electronic assists to medical records, including a cross-section of older patients with multiple comorbidities, and high-end consumers of health services and their acceptance to carrying their medical information, their interactions with health-care professionals and systems and how to study this. Finally, it is recognized that any clear result, whether positive or negative, from this trial will provide hypotheses for the future, as the technology used will be antiquated in a short time.

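### The 40 % discontinuation allowance is sized as if discontinuers leave the analysis, but the intention-to-treat analysis keeps them, so the stated 80 % power does not follow from the plan's assumptions

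*Protocol article*

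**What the plan says.** All references are to the protocol article.

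- **Sample size and power calculations.** The plan assumes that "at least 70 % of the subjects in the control arm would have at least one event" over 48 months, and it is sized "with the aim to detect a 25 % reduction in hospitalizations". At "80 % power and a 0.025 level of significance", this "requires 158 subjects per arm for analysis by a Fisher’s exact test of proportions". The next sentence begins "In order to provide for the loss of power due to patients discontinuing". It assumes 40 % dropout from the intervention arms, calls that the most cautious assumption, and arrives at 264 per arm and 792 in total.
- **Primary statistical analyses.** Each PHF arm is compared with usual care using an Andersen-Gill model for recurrent events. "The level of significance for each analysis is 0.025".
- **Methods: statistical analysis plan.** "All analyses will include all subjects randomized regardless of whether or when they may have withdrawn from the study".
- **Discussion.** The paragraph on limiting bias says that overnight hospitalization and death "will be ascertained regardless of whether a patient has withdrawn from the study". A later paragraph adds that the primary analysis takes in all patients whatever their compliance or their practitioners' adherence.

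**The concern.** Dividing by one minus the dropout rate is the right correction when dropouts supply no outcome data and are left out of the analysis. The number analysed falls back to the target and the effect among those analysed is unchanged.

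This trial does something else. A subject who stops using the PHF stays in the PHF arm, and that subject's hospitalizations and death still count. The number analysed stays at 264 and the average effect in the arm shrinks. The allowance corrects a quantity that does not change and leaves uncorrected the one that does. Nothing in the article reduces the 25 % effect for discontinuation.

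At stake is how the result is read. The reader is told that a 40 % discontinuation rate has been provided for at 80 % power. If that is not so, a neutral result may be given more weight as evidence of no benefit than the design supports.

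**Working it through.** **Inputs, all from the article.** Control-arm risk 0.70; relative reduction 25 %, so PHF risk 0.70 × 0.75 = 0.525; alpha 0.025 per comparison; power 0.80; Fisher's exact test; discontinuation 0.40. Sidedness is not stated. Two-sided is used because it reproduces the plan's figure.

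**Step 1: reproduce 158.** The uncorrected two-proportion formula is

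n₀ = [z₁₋α/₂ √(2p̄(1−p̄)) + z₁₋β √(p₁(1−p₁) + p₂(1−p₂))]² / (p₁−p₂)²

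With p̄ = 0.6125, z = 2.241 and 0.842, and difference 0.175:

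n₀ = (2.241 × 0.689 + 0.842 × 0.678)² / 0.0306 ≈ 146.0, or 147 after rounding up.

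The continuity correction, n = (n₀/4)[1 + √(1 + 4/(n₀ × 0.175))]², gives 157.3, or **158**. Enumerating every pair of outcomes, exact two-sided Fisher power at 158 per arm is **80.3 %**. One-sided 0.025 gives 121 (132 with the correction), so it is not what was used.

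**Step 2: reproduce 264 and 792.** 158/(1 − 0.40) = 263.3, rounded up to **264**; 3 × 264 = **792**. The allowance is therefore exactly the removal-from-analysis correction.

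**Step 3: power with everyone analysed.** Let r be the share of the 0.175 absolute benefit that discontinuers keep. PHF-arm risk is then

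p(r) = 0.60 × 0.525 + 0.40 × (0.70 − 0.175 r)

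Exact two-sided Fisher power, alpha 0.025, 264 per arm, control risk 0.70:

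| Benefit kept by discontinuers (r) | PHF-arm risk | Relative reduction | Power |
|---|---|---|---|
| 0 | 59.5 % | 15 % | 58.0 % |
| 0.25 | 57.75 % | 17.5 % | 73.0 % |
| 0.40 | 56.7 % | 19 % | 80.4 % |
| 0.50 | 56.0 % | 20 % | 84.6 % |
| 0.75 | 54.25 % | 22.5 % | 92.2 % |
| 1 (no dilution) | 52.5 % | 25 % | 96.6 % |

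Power crosses 80 % at r just above 0.39.

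**Step 4: sensitivity to when subjects stop.** The article gives no timing. Suppose, as an assumption, that the 40 % stop uniformly over 48 months, hazards are constant, and a discontinuer returns to the control hazard at once. Cumulative hazards over 48 months are −ln(0.30) = 1.204 (control) and −ln(0.475) = 0.744 (PHF). Averaged over stopping times, a discontinuer's risk is 0.619. PHF-arm risk is 0.60 × 0.525 + 0.40 × 0.619 = 0.563, and Fisher power is 83 %.

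**Step 5: sensitivity to control risk.** With the fullest dilution (15 % relative reduction) and 264 per arm, power is 58 % at a control risk of 70 %, 68 % at 75 %, 79 % at 80 % and 90 % at 85 %.

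**The case against.** A reader might infer that power simply falls to 58 % in the plan's own worst case. The article does not support that.

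- **The cautious label attaches to the 40 % rate, not to lost benefit.** The article does not say that discontinuers stop at the outset or gain nothing. The PHF is given to the patient already filled with a verified history (Additional procedures) and is used until the patient stops, so some exposure is expected. Stopping spread evenly over the trial gives about 83 % under the assumptions of step 4.
- **The 70 % is stated as a minimum.** The Discussion also reports that public hospital separations in older people rose by 12.9 % to 28.8 % after the data used for planning. A higher control risk raises power, as step 5 shows. The true rate is not given.
- **The primary analysis is not Fisher's test.** The plan calls Fisher conservative, and the Andersen-Gill model may have different power. That power cannot be computed here, because the article gives no recurrent-event rate for its population and no measure of within-subject variation.

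All three points stand, and they limit the 58 % to one end of a range. They do not rescue the allowance. The article makes none of these arguments in its support, dilution also acts on the Andersen-Gill estimate, and the factor 1/0.60 still belongs to an analysis that the article rules out. Reading the 40 % as lost outcome data does not help: the sample size section would then conflict with the statements that all randomized subjects are analysed and that hospitalizations and deaths are captured after withdrawal.

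**Conclusion.** The point holds in conditional form. The allowance does not match the analysis set, and 80 % power at 40 % discontinuation does not follow from what the article assumes. On the planning basis, power at 264 per arm runs from about 58 % (discontinuers at control-arm risk for the full 48 months) to about 97 % (no dilution). It reaches 80 % only if discontinuers keep roughly 40 % of the benefit or more.

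These figures rest on two-sided Fisher's exact test at 0.025, a 70 % control risk, the full 25 % reduction in those who continue, and complete capture of events after withdrawal. The article says that capture holds for hospitalizations and deaths, and it expects the remaining component, serious out-of-hospital events, to be rare.

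It does not follow that the trial is underpowered or needs more subjects. The retained benefit, the timing of discontinuation and the true control risk are unknown, and the power of the primary model was not computed.

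**What to change.** Keep 792 subjects. Replace the allowance sentence in Sample size and power calculations with text such as:

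> On the planning basis (two-sided Fisher's exact test, alpha 0.025, 70 % control-arm risk, 25 % reduction in those who continue), 264 per arm, all analysed, with 40 % of the PHF arm discontinuing, gives about 58 % power if discontinuers have control-arm risk for all 48 months, 73 % if they keep a quarter of the benefit, 85 % if they keep half, and 97 % with no dilution. Power is higher if the control-arm risk exceeds 70 % (for example, about 79 % at 80 % control risk with no retained benefit). Power of the Andersen-Gill primary analysis was not computed.

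The wording that calls 40 % the most cautious rate may stay, provided the text does not imply that 80 % power is assured at that rate.

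The cost is wording only: no extra subjects and no change to the endpoint, analysis set or test. The sponsor gives up a single favourable power figure for a range.

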### Ethics and governance

Informed consent will be obtained from each participant. The project has been approved by the South Eastern Sydney Local Health District Human Research Ethics Committee - Southern Sector (EC00135) reference number: 06/124 [name] (approval letter dated 8 December 2006). A recent amendment was approved (2 September 2014) to conduct exit interviews to obtain further qualitative data regarding the project. An IAC that includes a neurologist, a cardiologist, a rheumatologist and an infectious disease physician will evaluate all reported serious out-of-hospital events to determine whether they consider the event was a serious out-of-hospital event. All adjudications are undertaken blind to randomized arm status. The committee includes the Chief Investigator (ML) and project manager (SB) for administrative purposes only.

